### 5.1.2 Sensitivity analyses

Sensitivity analysis will be conducted for the primary endpoint as follows.

- The sensitivity of the estimated intervention effect to measured covariates of interest (centre, gestational age, birth weight, gender, mode of delivery (vaginal versus caesarean birth) and antenatal corticosteroid treatment) will be evaluated by regression modelling. Generalized estimating equations will be fitted to the primary endpoint, with predictors including treatment and the above covariates. The relative risk of occurrence of the primary endpoint will be calculated for intervention vs placebo after adjustment

|         |                                           |               |
|---------|-------------------------------------------|---------------|
| UCD CRC | SAP for the POPART trial                  |               |
| UCD CRC | Template: Statistical Analysis Plan (SAP) | Version: 1.0  |
|         |                                           | Page 14 of 19 |

for the above covariates using binomial generalized estimating equations with the small sample Kauermann and Carroll correction of the variance estimator used to calculate 95% confidence intervals around the relative risk.

- A competing risks model will be applied to investigate the effect of the intervention on the primary endpoint, adjusting for other outcomes that may impact on observation of the primary endpoint (e.g. death occurring before 120 hours of birth or intubation prior to 120 hours without meeting the criteria for respiratory failure defined in the protocol), should these competing risks occur.
- For infants intubated without meeting the pre-defined criteria for respiratory depression in the protocol, a sensitivity analysis will be conducted by assuming these infants would not have met the primary endpoint (i.e. as negative on the primary endpoint). Analysis will proceed as for the main analysis of the primary endpoint.
- A per protocol analysis of the primary endpoint will be conducted to determine whether the treatment effect is sensitive to protocol deviations. Analysis will proceed as for the main analysis of the primary endpoint.

### 5.1.3 Subgroup analyses

Subgroups of interest include infants of different gestational age strata (e.g. less than 26 weeks, and 26-28 weeks gestation at birth), and infants from different participating centres. Subgroup analysis of the primary endpoint and the important secondary outcome of death before hospital discharge will be carried out for these subgroups by:

- For each subgroup, the primary endpoint will be summarized per treatment arm by frequency and percentage, including the frequency of missing data. Relative risk of the primary endpoint will be estimated along with 95% confidence intervals for each subgroup, as per the main analysis of the primary endpoint.
- Log binomial regression of the primary endpoint will be conducted to evaluate interaction effects for treatment type and centre (if centre sample size permits), and for treatment type and gestational age, with the acknowledgement that this analysis is not likely to have sufficient statistical power.

## 5.2 Interim analyses

Interim analysis of the primary outcome and the important secondary outcome of death before hospital discharge will be performed on half of the planned sample (126) by a DSMB. The Haybittle-Peto boundary will be used as a stopping rule. Therefore, the DSMB may recommend terminating the study early for large and statistically significant differences ( $p < 0.001$ ) between groups in the primary outcome or in the important secondary outcome of death before hospital discharge; or for unanticipated concerns regarding the safety of enrolled infants.

### 5.2.1 Adjustment of Confidence intervals and p-values

The type I error rate for interim analysis will be set to 0.001 in accordance with the Haybittle-Peto stopping boundary. For final analysis, the type I error rate will be set at 0.05. Confidence intervals will be reported at a

|         |                                           |               |
|---------|-------------------------------------------|---------------|
| UCD CRC | SAP for the POPART trial                  |               |
| UCD CRC | Template: Statistical Analysis Plan (SAP) | Version: 1.0  |
|         |                                           | Page 15 of 19 |

95% confidence level.

### 5.3 Missing data

All data will be checked for missing values and followed-up to obtain data where possible. Missing data will be summarised by variable and by treatment arm. Spurious or anomalous data will also be queried and corrected if found to be incorrect. No data will be excluded as outliers.

For the handling of missing data, we will follow the flowchart given in . If there is few (<5%) or a lot (>40%) of missing data, we will only use the observed data for the analysis.

With a low frequency of missing data (<5%), we will also perform worst case/best case sensitivity analysis for the study endpoints.

With missingness between 5 and 40% missing data will be replaced using multiple imputation. Multiple imputations will be based on the randomization arm, and selected baseline, procedural and outcome variables (see below for selection criteria). Since missing values in these variables are possible, chained equations will be used (e.g. using mi impute chained in Stata or the mice package in R^4). This procedure fills in missing values in multiple variables iteratively based on a sequence of univariate imputation methods with fully conditional specification of prediction equations. Predictive mean matching will be used for continuous, logistic regression for binary, ordinal logistic regression for ordinal and multinomial regression for categorical variables (if applicable). Based on such chained equations, a total of 50 multiple imputations will be calculated. If it is not possible to impute all outcomes in one model, a stepwise approach will be considered. The 50 imputed data sets will be analysed using Rubin's rules.

Variables will be selected for inclusion in the imputation model using the following principles:

- Variables with more than 40% missing values will not be used
- Binary variables with a frequency of less than 5% in one category will not be used
- If two binary variables have less than 5% or more than 95% discordant pairs only one of the two will be used (the one with less missings).
- Levels of ordinal variables with a frequency of less than 5% will be collapsed by adding the entries to the neighbouring category (i.e. next higher or lower level) with the higher frequency (if there are more than one).
- Categorical variables might generally be recoded if it improves the fit of the imputation model and does not lead to substantial loss of information.
- Continuous variables will be log-transformed if it improves normality (checked by Shapiro-Wilk tests and QQ plots).

From the remaining variables an imputation model will be constructed based on combined clinical and statistical reasoning. All variables that may provide information about the imputed variable will be included.

|         |                                           |               |
|---------|-------------------------------------------|---------------|
| UCD CRC | SAP for the POPART trial                  |               |
| UCD CRC | Template: Statistical Analysis Plan (SAP) | Version: 1.0  |
|         |                                           | Page 16 of 19 |

#### 5.4 Safety evaluation

Adverse events will be summarized for each site and for the whole sample, including:

- Total number of adverse events
  - Number and percentage of adverse events that were serious (SAES)
  - Number and percentage of adverse events that were mild, moderate and severe
  - Number and percentage of treatment-related adverse events
  - Number and percentage of adverse events that were resolved without sequelae, resolved with sequelae, ongoing, or resulted in death.
- Number of deaths (all causes) per treatment arm
- Number of deaths resulting from adverse events per treatment arm
- Number and percentage of subjects experiencing
  - Any adverse event
  - Any serious adverse event
  - Mild, moderate and severe adverse events
  - Treatment-related adverse events

Further, any non-serious adverse event occurring with a greater than 5% frequency in either treatment arm, will be described by treatment arm, including:

- System organ class
- Event term
- Number of subjects per treatment arm affected by the event
- Total number of events of this type that occurred per treatment arm

For all serious adverse events (SAEs), the above information will be reported as well as:

- Number of these SAEs causally related to treatment, per treatment arm
- Number of these SAEs with fatal outcome, per treatment arm
- Number of treatment-related SAEs of this type with fatal outcome

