##### **Adverse events**

The number of adverse events (i.e. all events occurring, worsening or becoming serious after the randomisation), and the number and percentage of infants reported as having at least one emergent adverse event, will be reported by system organ class and preferred term, for each treatment group.

The same description will be performed for serious adverse events (SAE), severe AE, AE treatment related and AE leading to IMP withdrawal.

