## 6. Changes from the protocol

The SAP is consistent with the main features of the statistical methods described in the protocol.

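### SAP 5.4 leaves overall adverse event counts, severity and non-serious relatedness without a by-arm table, and limits non-serious terms by arm to those above 5%, where protocol 14.6 requires all of these by treatment group

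*Combined protocol and SAP*

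**What the plan says.** Protocol 14.6 (Adverse events) covers the number of events and the number and percentage of infants with at least one. These "will be reported by system organ class and preferred term, for each treatment group". It then asks for the same description of serious, severe and treatment-related events. It sets no frequency threshold.

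SAP 5.4 (Safety evaluation) has three parts:

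- **A general summary.** The lead-in is "Adverse events will be summarized for each site and for the whole sample, including". The list beneath it contains "Number and percentage of adverse events that were mild, moderate and severe" and "Number and percentage of treatment-related adverse events", the outcome of events, and the infants with any, any serious, mild/moderate/severe, or treatment-related events. None of these lines names an arm. Two lines do: "Number of deaths (all causes) per treatment arm" and the count of deaths resulting from adverse events.
- **Non-serious terms.** By-arm description applies to "any non-serious adverse event occurring with a greater than 5% frequency in either treatment arm".
- **Serious events.** Every serious term is reported by arm with no threshold, including the numbers causally related and fatal.

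SAP section 6 states: "The SAP is consistent with the main features of the statistical methods described in the protocol".

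**The concern.** The safety question is whether surfactant given into the oropharynx does more harm than giving nothing. Answering it requires the arms side by side, and SAP 3.2.3 keeps all control infants in the safety population for comparison. A count by site or for the whole sample cannot serve that purpose.

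Two features of the protocol add weight:

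- Protocol 13.4 limits reportable serious events to deaths and important medical events. A severe event can therefore be recorded as non-serious, and the SAP gives it no by-arm severity count.
- Protocol 13.3 waives reporting of events directly related to extreme prematurity. The remaining non-serious terms may be uncommon, which is where a 5% limit applies. The documents give no expected frequencies, so this is a possibility and not a finding.

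Protocol 14.1 requires the SAP to implement the protocol's main statistical features. Protocol 14.6 leaves only the definition of the Safety Set to be finalised in the SAP. A narrower by-arm safety report should therefore have been declared.

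**Working it through.** **1. The two texts compared**

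| Item | Protocol 14.6 | SAP 5.4 |
|---|---|---|
| Total adverse events | by group | site and whole sample |
| Infants with any adverse event | by group | site and whole sample |
| Infants with any serious event | by group | site and whole sample |
| Severity | severe events by group | site and whole sample |
| Treatment-related, non-serious | by group | site and whole sample |
| Treatment-related, serious | by group | by arm |
| Serious terms | by group | by arm, no threshold |
| Non-serious terms | by group, no threshold | by arm only above 5% in either arm |
| Deaths | within serious events | by arm |

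A non-serious term above 5% gets organ class, term, infants and events per arm, but not its severity or relatedness. Severity by arm appears nowhere in SAP 5.4.

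**2. Arm size**

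The point rests on text; the plan's sample size is used only to fix the denominator. Inputs from protocol 14.2 are 46% v 28%, two-sided 5% and 80% power; from 11.3.6, 1:1 allocation. With mean rate 0.37:

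n per arm = [1.960 × √(2 × 0.37 × 0.63) + 0.842 × √(0.46 × 0.54 + 0.28 × 0.72)]² / 0.18² = (1.338 + 0.565)² / 0.0324 ≈ 111.8, rounded up to 112.

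The total is 224, as the protocol states. 224 / 0.90 = 248.9, that is 249, against 250 stated. I assume 250 / 2 = 125 infants per arm, all treated as allocated.

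**3. What the 5% limit means**

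0.05 × 125 = 6.25, so a term needs at least 7 infants in one arm to be described by arm. Two-sided Fisher exact tests:

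| Surfactant v control (of 125 each) | p | By arm under SAP 5.4? |
|---|---|---|
| 5 v 0 | 0.060 | no |
| 6 v 0 | 0.029 | no |
| 6 v 1 | 0.12 | no |
| 7 v 0 | 0.014 | yes |

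If a non-serious term never occurs in controls, the chance that it is described by arm is P(X ≥ 7), with X binomial (125, true surfactant rate):

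| True surfactant rate | Chance of by-arm description |
|---|---|
| 3% | 8% |
| 5% | 43% |
| 8% | 88% |
| 10% | 97% |

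With 112 per arm, 0.05 × 112 = 5.6, so the threshold is 6 infants and the largest undescribed split is 5 v 0 (p = 0.060).

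**4. What pooling conceals**

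Assumed counts: 20 infants with a severe event among 250. The whole-sample line reads 20/250 = 8.0% for each of these splits:

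| Split | Fisher p |
|---|---|
| 10 v 10 | 1.00 |
| 15 v 5 | 0.034 |
| 20 v 0 | < 0.001 |

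**The case against.** A reader might infer that the SAP replaces by-arm safety reporting altogether, discards rarer events, and so cannot reveal an excess of severe or related events. The documents do not support that:

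- Deaths, all serious terms, related and fatal serious events, and non-serious terms above 5% are by arm.
- Terms at or below 5% stay in the totals. They lose only the by-term, by-arm description.
- Control infants receive nothing into the oropharynx, so events attributed to study medication should arise almost only in the surfactant arm. Pooling non-serious related events hides little.
- Pneumothorax, pulmonary haemorrhage, intraventricular haemorrhage and BPD are waived as adverse events but compared by arm as secondary endpoints.
- Severe events that are serious, or belong to terms above 5%, would still show by arm through those terms. The example in step 4 bites fully only for severe events that are non-serious and spread over rare terms.
- At 125 per arm, 6 v 0 is the only excess in surfactant infants below the cut-off with p under 0.05, before any allowance for the number of terms examined.

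All of this stands, and it narrows the point.

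It can also be argued that the lead-in only sets the level of aggregation, and that protocol 14.6 and the safety board's review of both groups (13.5) already secure the comparison. This is weaker. The authors wrote the arm label on some lines of the same list and not on others, so it cannot safely be read in. Board review during the trial is not the final analysis. A protocol requirement does not correct SAP tables specified differently. A drafting slip is possible, but nothing in the text says so.

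**Conclusion.** The point holds for a defined set of items. SAP 5.4 does not provide by-arm reporting of total adverse events, infants with any adverse event or any serious event, severity, or non-serious treatment-related events. It also restricts by-arm description of non-serious terms to those above 5%. Protocol 14.6 requires these by treatment group without a cut-off, and SAP section 6 does not declare the difference. This is a conflict between stated rules, not a missing detail.

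The main loss is the comparison of severity and of overall event burden. The loss for related events is small. The 5% limit matters at the margin: 6 v 0 is not described by arm, and a term with a true 5% rate confined to surfactant infants has a 43% chance of being described. These figures assume 125 treated infants per arm and no such events in controls; the severe-event counts are illustrative. Efficacy conclusions are unaffected.

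**What to change.** - In the SAP 5.4 lead-in, specify the summary *by treatment arm and overall*. Apply this to the lines for total events, infants with any event, infants with any serious event, severity and relatedness. Keep the site table as an addition.
- Give all adverse event terms by system organ class and preferred term per arm, as protocol 14.6 states. Otherwise declare the 5% limit in SAP section 6 and justify it.
- Confidence intervals for between-arm differences are optional; protocol 14.6 does not ask for them.
- If the analysis has already been run to SAP 5.4, produce the protocol 14.6 tables and describe the deviation in the final report under protocol 14.10.

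The cost is SAP wording and longer tables. No new data are needed.

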#### 5.5 Statistical software

The statistical analysis will be performed using the statistical software packages Stata and/or R^4.

#### 5.6 Quality control

An independent statistician will conduct all analysis of the primary endpoint and key secondary endpoints. A statistician at UCD CRC will reproduce the primary of the primary endpoint based on the exported data as a quality control check. P-values of the primary analysis of the primary endpoint should be the same and limits of

|         |                                           |               |
|---------|-------------------------------------------|---------------|
| UCD CRC | SAP for the POPART trial                  |               |
| UCD CRC | Template: Statistical Analysis Plan (SAP) | Version: 1.0  |
|         |                                           | Page 17 of 19 |

the corresponding 95% confidence interval should not differ by more than 0.5 percentage points. Otherwise, the reason for the difference will be determined and a consensus must be reached.

|         |                                           |               |
|---------|-------------------------------------------|---------------|
| UCD CRC | SAP for the POPART trial                  |               |
| UCD CRC | Template: Statistical Analysis Plan (SAP) | Version: 1.0  |
|         |                                           | Page 18 of 19 |

## 6. Changes from the protocol

The SAP is consistent with the main features of the statistical methods described in the protocol.

